# Evaluating air leakage from staple line reinforcements in anatomical pulmonary resection (AIRSTOP): a prospective randomized controlled trial protocol

**DOI:** 10.1007/s11748-024-02111-0

**Published:** 2024-12-26

**Keywords:** Air leakage, Anatomical pulmonary resection, Staple line reinforcement

## Abstract

**Background:**

Air leakage during pulmonary resection is a major complication in thoracic surgery. It frequently occurs at sites of adhesion dissection, due to lung manipulation, and along the staple lines of automatic suturing devices, particularly in cases of pulmonary fragility such as those of emphysema and interstitial pneumonia. Persistent postoperative air leakage prolongs chest tube indwelling and extends hospitalization time. Staplers with absorbable tissue reinforcements have been introduced for pulmonary resection to prevent intraoperative stapler-related air leakage. This phase II prospective, open-label, randomized, parallel-group trial aims to validate the efficacy of staplers with or without absorbable tissue reinforcements in controlling stapler-related air leakage during anatomical pulmonary resections.

**Methods:**

Overall, 120 patients will be randomized into two groups: one that will undergo conventional anatomical pulmonary resection and the other in which staplers with absorbable tissue reinforcements will be used. The primary endpoint will be intraoperative stapler-related air leakage. Data will be analyzed between 2024 and 2025.

**Discussion:**

This trial will validate the effectiveness and safety of staple line reinforcements in controlling intraoperative air leakage during anatomical pulmonary resections, potentially leading to optimized strategies for patients with conditions such as emphysema and interstitial pneumonia.

**Trial registration:**

This trial has been registered with the Japan Registry of Clinical Trials 1032220620 (https://jrct.niph.go.jp/latest-detail/jRCTs031230224).

## Introduction

### Background

Air leakage is a common postoperative complication of anatomical pulmonary resection, often resulting from lung injury during intraoperative manipulation [1, 2]. It is particularly prevalent at sites of adhesion dissection and along the staple lines of automatic suturing devices [3].

### Rationale and knowledge gap

Staplers with absorbable tissue reinforcements, such as those made from polyglycolic acid or glycolic acid–lactic acid polyester, have been introduced to reduce air leakage along staple lines [4–7]. This innovation is anticipated to reduce intraoperative air leakage, thereby shortening the time required for repair, chest tube replacement duration, and overall hospital stay. However, the superiority of staplers with absorbable tissue reinforcement over conventional staplers has not been systematically evaluated.

### Objective

This trial aims to assess the efficacy and safety of staplers with absorbable tissue reinforcement for controlling intraoperative and postoperative air leakage during anatomical pulmonary resection.

## Methods

### Study design and objectives

#### Preoperative findings

This prospective, randomized controlled trial will include patients with pulmonary diseases who require anatomical pulmonary resection. Routine preoperative examinations will be performed to confirm patient eligibility, and eligible patients will be required to provide informed consent. The study schema is presented in Fig. 1, and the measurement schedule is summarized in Table 1.

**Fig. 1 Fig1:**
[figure not shown]
Design of the clinical trial

**Table 1 Tab1:** Detailed measurement schedule

	Enrollment	Observation period		
		Operative day	After operation	Follow-up (until POD 42)
Informed consent	●			
Clinical findings	●	●	●	●
Background information	●			
Initial vital signs	●			
Spirometry	●			
Complete blood count, Biochemical testing	●		●	●
Chest X-ray	●	●	●	●
Chest CT	●			
Presence of intraoperative stapler-related air leakage (Primary endpoint)		●		
Time to repair intraoperative air leakage (Secondary endpoint)		●		
Number of automated suturing devices used in pulmonary resection (Secondary endpoint)		●		
Air leakage, due to surgical procedures (Secondary endpoint)		●	●	●
Duration of postoperative chest drain tube placement (Secondary endpoint)			●	
Presence of postoperative prolonged air leakage (Secondary endpoint)			●	
Presence of additional procedures (Secondary endpoint)			●	●
Presence of delayed air leakage (Secondary endpoint)			●	●
Postoperative adverse event (Secondary endpoint)		●	●	●

A black dot indicates a mandatory survey

*POD* Postoperative day, *Biochemical testing* measurement of glycosylated hemoglobin, albumin, and Krebs von den Lungen 6, *CT* Computed tomography

##### Inclusion criteria

Patients aged 18 years or older who were scheduled to undergo anatomical pulmonary resection (lobectomy or segmentectomy) using an automatic suturing device;Patients with incomplete interlobar fissures on preoperative chest computed tomography (CT) who were considered to require pulmonary resection involving the use of an automatic suturing device;Patients with preserved main organ function and an Eastern Cooperative Oncology Group (ECOG) performance status of 0–1; andPatients fully informed of the study and who provide informed and voluntary written consent for participation.

##### Exclusion criteria

Patients undergoing pulmonary partial resection or requiring multiple lobectomy or segmentectomy;Patients who were considered to have complete interlobar fissures on preoperative chest CT and not to require pulmonary resection involving the use of an automatic suturing device;Patients with dementia or other conditions that require consent from their legally authorized representatives; andPatients with known allergies to the study materials or deemed by the investigator to be unsuitable for safe participation in this study.

Incomplete interlobar fissures refer to a situation where the fissures (natural separations between lobes) in the lungs are not fully formed or do not completely divide the lung lobes.

#### Sample size

A total of 120 patients will be recruited. The recruitment period extends from January 2023 to December 2025. The presence or absence of intraoperative air leakage in the staple line reinforcement and non-use groups will be investigated. Based on the results of a retrospective study conducted at our institution, the expected intraoperative air leakage rates in the staple line reinforcement group and group without staple line reinforcement are 27% and 50%, respectively. With a significance level of 5%, power of 70%, and a 1:1 allocation between the groups, 55 patients have been estimated to be required in each group. Considering ineligible cases and dropouts, the enrollment of 60 patients in each group has been planned.

#### Participants and randomization

The patients will be enrolled before surgery and randomly allocated to four groups. The allocation process is based on the use of an automatic suturing device equipped with staple line reinforcements (absorbable tissue reinforcement composed of polyglycolic acid or glycolic acid–lactic acid polyester) versus a conventional automatic suturing device. Sex and procedure (lobectomy or segmentectomy) will be used for allocation to the following four groups: These factors have been selected because factors confounding sex such as respiratory function, smoking history, and general frailty, may influence lung fragility, and the number of automatic suturing devices planned for use may differ according to the procedure. Random allocation will be performed at a 1:1 ratio, with central registration at an independent data center, to minimize selection bias. The schematic of the study is shown in Fig. 1. Allocation for groups A and B will be achieved based on the aforementioned factors, whereas that for subgroups A1, A2, B1, and B2 was random and equal. The following devices were used in the groups:

Group A: Automatic suturing device with staple line reinforcement;

Subgroup A1: Powered ECHELON FLEX as the automatic suturing device, Tri-Staple cartridge, and ECHELON ENDOPATH^®^ Staple Line Reinforcement (ECHICON Johnson & Johnson, NY, U.S.A.) used for absorbable tissue reinforcement;

Subgroup A2: Signia Stapling System as the automatic suturing device and Tri-Staple 2.0 Reinforced Reload^®^ (Medtronic, Dublin, Ireland) used for absorbable tissue reinforcement;

Group B: Conventional automatic suturing device;

Subgroup B1: Powered ECHELON FLEX as automatic suturing device and Tri-Staple cartridge; and

Subgroup B2: Signia Stapling System as the automatic suturing device and Tri-Staple2.0.

The appropriate stapler size will be selected by the surgeon, based on the thickness and rigidity of the lung tissue to be resected.

### Procedure

#### Intraoperative findings

Factors such as background lung (presence of emphysema or interstitial pneumonia), presence of adhesions, operative time, blood loss, presence of interoperative air leakage, and time to repair pulmonary air leakage, will be assessed. Surgical cases in which the use of an automatic suturing device is judged to be not required for pulmonary resection and those considered unsuitable for en bloc resection were considered ineligible.

After pulmonary resection, a standard water-seal test will be conducted, beginning at an airway pressure of 15 cm H₂O and progressing to a maximum pressure of 20 cm H₂O. The presence, location, and extent of air leakage due to intraoperative manipulation, such as that at the staple line site, will be assessed. If air leakage is observed, its location and extent will be documented and the time required for repair (in minutes) will be recorded.

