### Statistical analysis

For the primary endpoint, proportions were calculated and comparisons between groups were performed using the chi-square test. To supplement the analysis of the primary endpoints, we also analyzed the secondary endpoints. No multiplicity adjustments were made in the analysis of secondary endpoints. For each secondary endpoint, group comparisons were conducted using a *t* test for continuous variables and the chi-square test or Fisher's exact test for categorical variables.

The safety endpoint was the frequency of adverse events; we recorded the frequency and proportion of adverse events, created a list of these, and calculated the frequency. All comparisons were planned and all *p* values were two sided. Statistical significance was set at *P* < 0.05. All statistical analyses were performed using the SAS software (version 9.4; SAS).

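### Patients are randomised before open-label surgery, but a judgement in theatre can then make them ineligible, so an arm-aware exclusion could bias the primary comparison in either direction

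*Protocol article*

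**What the plan says.** All references are to the protocol article.

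- **Abstract, Background:** the design is "This phase II prospective, open-label, randomized, parallel-group trial".
- **Participants and randomization:** "The patients will be enrolled before surgery and randomly allocated to four groups". The arms differ by device (reinforced or conventional stapler), so the operating team can know the assignment.
- **Exclusion criteria:** need for a stapler is already screened before enrolment. The criteria exclude "Patients who were considered to have complete interlobar fissures on preoperative chest CT" and who are not expected to need stapled division.
- **Procedure, Intraoperative findings:** a second judgement follows, now in theatre. One category is "Surgical cases in which the use of an automatic suturing device is judged to be not required for pulmonary resection". The other is cases in which en bloc resection proves unsuitable. Both are declared ineligible. The water-seal test is described afterwards, as a step that follows resection.
- **Sample size:** the calculation gives 55 per group, and then "Considering ineligible cases and dropouts, the enrollment of 60 patients in each group has been planned".
- **Statistical analysis:** the primary endpoint is compared by chi-square test. No analysis set is named.

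**The concern.** Central randomisation protects against selection up to the moment of allocation. It cannot protect against a selection step that comes later and is made by people who may know the arm. The in-theatre judgement is such a step, and the sample-size allowance shows that the plan expects to lose patients to it.

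The judgement is also related to prognosis. Whether stapled division is needed depends on the fissure and lung found at operation. The article itself links lung fragility to leakage (Discussion) and expects the number of staplers to vary with the procedure (Participants and randomization). A patient in whom no stapler is fired cannot have the primary event, stapler-related leakage. A patient unsuitable for en bloc resection may well have been stapled and may have leaked.

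If the threshold for either judgement shifts with the known device, the two analysed groups are no longer comparable and the chi-square p-value loses its usual meaning. Nothing shown requires the judgement to be blinded, made against objective criteria, or recorded before the allocation is known.

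**Working it through.** **1. The plan's own figure.** Inputs from Sample size: 27% and 50%, "With a significance level of 5%, power of 70%, and a 1:1 allocation between the groups". From Statistical analysis: p "values were two sided". Pooled-variance formula without continuity correction, with mean rate 0.385:

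n = [1.960 × √(2 × 0.385 × 0.615) + 0.524 × √(0.27 × 0.73 + 0.50 × 0.50)]² / 0.23²
= [1.960 × 0.688 + 0.524 × 0.669]² / 0.0529 = 54.6, so 55 per group.

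The stated 55 is reproduced. The step to 60 allows a loss of 5/60 = 8.3% per group, for ineligible cases and dropouts combined. The sample-size arithmetic is sound.

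**2. How far one exclusion moves the test.** The counts are invented for illustration: 20/60 reinforced and 30/60 conventional. Pearson chi-square = N(ad − bc)² / (product of the four margins), no correction.

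| Reinforced arm (against 30/60) | What happened | Chi-square | p |
|---|---|---|---|
| 20/60 | nobody excluded | 120 × 600² / (60 × 60 × 50 × 70) = 3.43 | 0.064 |
| 19/59 | one leaker excluded | 119 × 630² / (59 × 60 × 49 × 70) = 3.89 | 0.049 |
| 20/59 | one non-leaker excluded | 119 × 570² / (59 × 60 × 50 × 69) = 3.17 | 0.075 |
| 19/60 | one would-be leaker not stapled, kept as a non-event | 120 × 660² / (60 × 60 × 49 × 71) = 4.17 | 0.041 |

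Rows two and three show that a single exclusion can move the result either way. Row four matters for the remedy: keeping no-stapler cases as non-events does not undo a stapling decision that was itself influenced by the arm.

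**3. Outer bound on false positives.** Assume no true effect, 60 per arm, and five would-be leakers removed from one arm only, picked perfectly. Under a normal approximation, the two-sided error rises from 5% to about 7.7% (common leak rate 50%) or 13.1% (common leak rate 27%). By symmetry this holds whichever arm loses them. It is an extreme, not a forecast.

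**4. Power if everyone is kept.** Assume the whole allowance, 5 of 60 in each arm, consists of no-stapler cases counted as non-events. The rates become 0.27 × 55/60 = 24.75% and 0.50 × 55/60 = 45.8%. Exact binomial enumeration of the chi-square test gives:

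- 55 evaluable per arm, 27% against 50%: 71.0%
- 60 per arm, 24.75% against 45.8%: 68.5%

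The normal approximation gives 70.3% and 68.0%, and about 63 per group to regain 70%.

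**The case against.** A reader might infer more than the documents support, in three ways.

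*That the protocol expressly removes these patients from the primary analysis.* It does not. It calls them ineligible and adds patients to cover ineligible cases and dropouts. Removal is a reasonable inference from those two statements, but a statistical analysis plan not shown here could keep them. What remains is that the protocol states the rule and plans for the loss. An analysis plan that kept these patients would need to be reconciled with it.

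*That the surgeon excludes after seeing the leak.* The water-seal test is placed after resection, so the judgement probably comes first, although no deadline is given. The concern does not need the leak to have been seen. Knowledge of the arm plus a link to prognosis is enough.

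*That the bias favours reinforcement.* Nothing shows this. Patients with complete fissures and no staple line are non-events, and removing them from the reinforced arm moves the result away from significance (20/59, p=0.075). Preoperative CT screening should also keep the number of such cases down, and no expected number is given.

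Excluding patients who could not have the event may also seem natural. That is harmless only if the decision is independent of arm, which an open-label design cannot assure. It does not cover the en bloc route at all.

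**Conclusion.** The concern holds. The protocol states an eligibility judgement that follows randomisation and can be made knowing the arm. If the cases it labels ineligible are dropped, the primary comparison can be biased in either direction.

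The size of the bias cannot be derived from the documents, and there is none if exclusions are unrelated to arm. The 8.3% allowance is only a planning guide: it also covers dropouts and does not cap exclusions. The illustration shows that one discretionary exclusion can carry a borderline result across 0.05. It does not show that this will happen.

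**What to change.** **Patients still to be enrolled** (recruitment is stated to run to December 2025). Have the data centre disclose the allocation only after the in-theatre eligibility judgement has been recorded. This removes the arm-aware judgement at its source.

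**Patients already randomised.** Define the primary analysis as all randomised patients who undergo surgery, in the arm assigned. Cases unsuitable for en bloc resection keep their observed water-seal result. Cases with no stapler fired count as having no stapler-related leak. Present the analysis that excludes ineligible cases as a sensitivity analysis, and report exclusions by arm and reason.

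**Limit to state.** Counting no-stapler cases as non-events does not correct a stapling threshold that shifts with the known device (19/60 in the example, p=0.041). Only later disclosure deals with that, which is why the number of no-stapler cases by arm should be shown.

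**Cost.** The analysis change is a matter of wording. Later disclosure changes the registration procedure and leaves two timings of allocation in one trial, which should be reported. If 5 of 60 per arm are no-stapler cases, power is about 68.5%, below the planned 70% and below the 71.0% obtained with 55 evaluable per arm. The stated power should be revised accordingly.

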### Endpoints

The primary endpoint is the incidence of intraoperative stapler-related air leakage. Air leakage assessed in this study will be categorized as follows: stapler-related air leakage and air leakage not caused by the stapler. Stapler-related air leakage is defined as air leakage that is considered to have been caused by invasion with an automatic suturing device during pulmonary resection (e.g., staple holes, stamps, staple line overlapping sites, and pleural defects near the staple lines). Air leakage not caused by a stapler is defined as air leakage not caused by an automatic suturing device (e.g., pleural defects due to adhesion dissection and lung injury grasping during surgery).

The secondary endpoints are as follows: (1) time required to repair the intraoperative air leakage; (2) duration of postoperative chest tube placement; (3) use of additional procedures; (4) incidence of delayed air leakage; (5) incidence of intraoperative air leakage due to automatic suturing devices; (6) incidence of intraoperative air leakage, postoperative air leakage, and delayed air leakage during surgical procedures; and (7) number of automatic suturing devices used in pulmonary resection.

Other postoperative adverse outcomes will be confirmed as the safety endpoint.

The exploratory issues are as follows: (1) preoperative clinical diagnosis; (2) pathological diagnosis; (3) comorbidity; (4) intraoperative approach (video-assisted thoracic surgery (VATS), hybrid VATS, and open thoracotomy); (5) surgical duration (min); (6) method of the procedure if the procedure was performed for a persistent air leakage; (7) duration of postoperative hospital stay (days); (8) concomitant medications; (9) respiratory function tests; and (10) evaluation of emphysema by measuring the low attenuation volume in lung field analysis using 3D-CT images.

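### Repair time, a secondary endpoint compared by t test, exists only for patients who leaked, so as written the comparison gives no credit for repairs avoided

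*Protocol article*

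**What the plan says.** All references are to the protocol article.

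- **Recording (Intraoperative findings).** After the water-seal test: "If air leakage is observed, its location and extent will be documented and the time required for repair (in minutes) will be recorded". This applies to any leak seen, not only stapler-related ones.
- **Status (Endpoints).** The list of secondary endpoints opens with "1) time required to repair the intraoperative air leakage".
- **Test (Statistical analysis).** "For each secondary endpoint, group comparisons were conducted using a *t* test for continuous variables". P values are two-sided, and secondary endpoints are not adjusted for multiplicity.
- **Expected leak rates (Sample size).** "the expected intraoperative air leakage rates in the staple line reinforcement group and group without staple line reinforcement are 27% and 50%, respectively".
- **Schedule (Table 1).** Repair time is marked as required on the operative day. No entry says what is recorded when there was nothing to repair.

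Nowhere does the article give patients without a leak a value, or say which patients enter the repair-time comparison.

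**The concern.** A time in minutes that is recorded only after a leak does not exist for patients who did not leak. A t test on the recorded times then compares leakers with leakers. Leaking is close to the primary endpoint itself, and the trial is sized on the expectation that treatment changes it. The two sets of leakers are therefore not protected by randomisation, and the difference between them depends on which leaks the reinforcement prevents.

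What is at stake is whether the endpoint answers its own question. The Introduction names a shorter repair time among the expected benefits, and the Discussion hopes for less operating time spent on leak repair. A prevented leak saves its whole repair time, yet the patients in whom that happened are the ones who drop out of the comparison.

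**Working it through.** **1. The article's own figure.** Inputs from Sample size: 27% vs 50%, 5% significance (two-sided, from Statistical analysis), 70% power, 1:1. With the pooled-variance formula and mean rate 0.385:

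n = [1.960·√(2·0.385·0.615) + 0.524·√(0.27·0.73 + 0.50·0.50)]² / 0.23² = (1.349 + 0.351)² / 0.0529 ≈ 54.6, so 55 per group.

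This matches "55 patients have been estimated to be required in each group", so the rates can be taken as the design assumption.

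**2. Who has a repair time.** Reinforced: 55 × 0.27 = 14.9. Conventional: 55 × 0.50 = 27.5. That is about 42 of 110 patients (16 and 30 at 60 per group). These counts assume that 27% and 50% cover all leaks. If they refer to stapler-related leaks only, other leaks add to both groups.

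**3. What the leakers-only difference estimates.** Assume that 27% of patients leak with either device (mean repair time R, the remaining leaks) and 23% leak only without reinforcement (mean P, the prevented leaks). Reinforced minus conventional:

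- Among leakers: R − (0.27R + 0.23P)/0.50 = 0.46(R − P).
- Per randomised patient, no leak = 0: 0.27R − (0.27R + 0.23P) = −0.23P.

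The second is always negative, that is, in favour of reinforcement. The first is zero if R = P and positive only if R > P. With R = P, repair time per patient falls by 1 − 0.27/0.50 = 46%, and the leakers-only comparison has nothing to detect.

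**4. Assumed minutes.** The documents give no repair times, so R and P are assumptions. The last column comes from 5,000 simulated trials per row, with 55 per arm and gamma times with coefficient of variation 0.6.

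| R / P (min) | Leakers only (min) | Per patient (min) | Reinforcement looks longer among leakers (significantly) |
|---|---|---|---|
| 15 / 5 | 15.0 vs 10.4 | 4.05 vs 5.20 | 94% (38%) |
| 10 / 5 | 10.0 vs 7.70 | 2.70 vs 3.85 | 89% (25%) |
| 10 / 7.5 | 10.0 vs 8.85 | 2.70 vs 4.43 | 72% (9%) |
| 10 / 10 | 10.0 vs 10.0 | 2.70 vs 5.00 | 49% (3%) |
| 5 / 10 | 5.0 vs 7.30 | 1.35 vs 3.65 | 4% (0%) |

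**5. A second model, to show the range.** Conventional arm: 25% small leaks (5 min) and 25% large leaks (15 min). Lognormal times with log-SD 0.4, 55 per arm.

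- *Small leaks cut to 2%, large unchanged.* Among leakers: (0.02·5 + 0.25·15)/0.27 = 14.3 vs (0.25·5 + 0.25·15)/0.50 = 10.0 min. Per patient: 3.85 vs 5.0 min. Wrong sign in 98% of trials, significantly wrong in 48%. With log-SD 0.7 these fall to about 89% and 25%.
- *Both kinds cut in proportion (13.5% each).* Among leakers: 10.0 vs 10.0 min. Wrong sign in about 50%.
- *Large leaks cut to 2%, small unchanged.* Wrong sign in under 1%, correctly significant in about 61%.

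**6. Scoring no leak as 0.** In the first case of step 5, the sample mean per patient favours reinforcement in about 80% of trials. If all leaks take equally long, a rank test on all patients has about 66% power. That is close to the planned 70% for the primary comparison, because with about 73% and 50% zeros the test mostly re-detects leak versus no leak.

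**The case against.** The strongest reply is that the leakers-only analysis is inferred. The recording sentence concerns data collection, since a repair can be timed only if there was one. The Statistical analysis section does not restrict the t test to leakers, and Table 1 marks repair time as required for the operative day. A full protocol or analysis plan, not shown, might score no leak as 0 minutes. This stands to a degree: leakers-only is the natural reading, not an explicit one. It does not remove the point. The article states both the recording rule and the test, and together they lead to that comparison. If zeros were intended, a plain t test would face data that are 73% and 50% zeros.

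A reader might infer that the endpoint will make an effective device look worse. The documents do not support that. They contain no repair times or leak sizes, and the definition of stapler-related leakage includes overlap sites and nearby pleural defects, so nothing shows that only small leaks would be prevented. Non-stapler leaks dilute the effect too: adding an assumed 20% of such leaks at 8 min to both arms lowers the 98% and 48% to 85% and 18%.

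It is also fair that the lower leak rate would be reported alongside, so readers would still see that leaks were prevented, and that time among leakers has descriptive value.

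**Conclusion.** The point holds, as something that should be fixed in one secondary endpoint. As written, the t test compares patients selected by an outcome that treatment is expected to change, and it cannot credit repairs avoided. The firmest result needs only the article's two rates and equal repair times: an expected difference of zero among leakers against a 46% lower repair time per patient. Reversal is conditional. It requires the prevented leaks to be quicker to repair than the remaining ones, and the illustrative wrong-sign rates run from 98% through about 50% to under 1%, depending on assumed minutes.

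It would go too far to conclude that the trial's main result is compromised. The primary endpoint, its chi-square test and the 55 per group are untouched, the secondary endpoints are supplementary and unadjusted, and being listed first gives repair time no formal priority.

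**What to change.** 1. Define the endpoint as total leak-repair minutes per randomised patient, with 0 for patients without a leak. State whether it covers all leaks or only stapler-related ones.
2. Make the between-group difference in mean minutes per patient the main comparison, with a bootstrap or permutation interval or test. A rank test is less useful here because it mostly repeats the leak/no-leak comparison.
3. Report times among patients who leaked descriptively, by group, alongside the number who leaked.

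The cost is wording in the protocol or analysis plan, settled before the groups are compared. No new data are needed, because leak status and repair time are already collected. The downside is that the zero-scored endpoint overlaps with the primary endpoint and is noisy at this sample size, so it should be read as an estimate of time saved and not as independent confirmation.
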